## 3. Results

Participants will undergo two assessments, one at the beginning of the PE program and one at the end, consisting of three stages: (i) body composition assessment; (ii) cardiovascular response assessment; and (iii) cardiorespiratory fitness assessment.

### 3.1. Instruments

#### 3.1.1. Anamnesis Form

The anamnesis form to be applied will contain personal identification and health information; a characterization of development and limitations; and a description of the therapeutic path and sporting past [32], which will be completed by the institutional psychologist.

#### 3.1.2. Anthropometric Measurements

Anthropometric measurements will be taken separately in a private room, following standardized procedures [33,34].

##### Height

To measure body mass and height, a scale with a retractable wall stadiometer model 206 (Seca GmbH & Co. KG, Hamburg/Germany) with a gradation of 1 mm. The participant stands barefoot, in a straight position, with the upper limbs alongside the body, feet joined at the heels, and the tips of the feet slightly apart, placing the vertex (upper part of the skull) in the highest position. Subsequently, the body mass index (BMI) will be calculated using the formula
Weight (kg)/Height (m)^2^(1)

##### Waist Circumference

To measure waist circumference, a 2 m Holtain (Holtain Limited, Crymych/UK) plastic tape measure with an accuracy of 1 mm will be used directly on the skin. Once in the anatomical position, the perimeter will be measured at the midpoint between the lower margin of the tenth rib and the iliac crest [35].

#### 3.1.3. Body Composition

The Inbody 770 (InBody Co., Ltd, Seoul/South Korea), an advanced bioimpedance device that assesses body composition with proven precision, will be used. It is an ideal tool for ongoing research, as it covers an age range of 3 to 99 years, and is also a safe, non-invasive, and fast method. In this sense, it is a technology that uses direct segmental multi-frequency bioimpedance (DSM-BIA) measurement, a tetrapolar system with eight electrodes, which varies the frequency from 1 to 1000 KHz, with an approximate measurement time of 60 s [36].

The following parameters will be obtained from the assessment: total body water; extracellular water; intracellular water; bone mineral content; degree of obesity; body composition history; impedance and reactance of each segment; total and segmental body phase angle; body and segmental edema index; body fat index; fat-free mass index; body cell mass; lean mass of each body segment; estimated segmental fat; skeletal muscle mass; minerals; visceral fat level; body fat percentage; protein; waist-to-hip ratio; and basal metabolic rate.

The participant should climb onto the equipment platform barefoot to establish contact with the four electrodes on their feet. After being prompted by the device, they should take the two electrodes in their hands and move their upper limbs away from their torso, maintaining this position and looking straight ahead.

#### 3.1.4. Functional Profile

##### Childhood Autism Rating Scale

To characterize the profile and level of severity of the participant’s disorder, the Childhood Autism Rating Scale (CARS) instrument will be used [37,38] to be completed by the clinical psychologist who accompanies the individuals in the referral service. This study will use the CARS2-ST to assess the functionality of the sample group up to the age of 16, which was validated and translated into Portuguese by Pereira et al. [39].

This scale evaluates behaviors in 14 domains generally affected by autism spectrum disorder, added to a single category for the description of general impressions [40,41]. The 15 assessment items are as follows: (1) interaction with people; (2) imitation; (3) emotional response; (4) use of the body; (5) use of objects; (6) adaptation to change; (7) reaction to visual and (8) auditory stimuli; (9) response to and use of taste, smell and touch; (10) fear or nervousness; (11) verbal communication; (12) non-verbal communication; (13) activity level; (14) coherence of intellectual response; and, finally, (15) general impressions. The score assigned to each domain ranges from 1 (within normal limits) to 4 (severe autistic symptoms). The total score ranges from 15 to 60, and the cut-off point for ASD is 30 [42].

##### Autism Spectrum Quotient (ASQ)

In order to measure functionality in the remaining group (adults aged 16 and over), the Portuguese version of the Autism Spectrum Quotient (AQ) form will be used, adapted by São Luís Castro and César Lima at the Speech Laboratory of the Faculty of Psychology and Educational Sciences of the University of Porto [43].

The original version of the AQ [44] is simple to apply and provides a measure to quantify the presence of autistic traits. It consists of a questionnaire of 50 statements about five different areas in which pathologies within the disorder have a distinct profile (social skills, attention modulation, attention to detail, communication, and imagination), in which the participant or clinical psychologist is asked to answer whether they totally agree, slightly agree, slightly disagree or totally disagree, with 1 point being given to hypotheses directed towards typically autistic behavior and 0 points to the rest, obtaining a maximum score of 50 points.

#### 3.1.5. Cardiovascular Response

The Omron Digital Blood Pressure Monitor HEM-907 digital sphygmomanometer (Omron Healthcare Europe BV, Matsusaka/Japan) will be used to measure hemodynamic parameters such as systolic blood pressure (SBP), diastolic blood pressure (DBP), and resting heart rate (RHR). Before data collection, participants will remain completely at rest for 5 min, with their legs uncrossed, back and arms supported, without talking and/or moving [45]. Participants will be instructed to sit comfortably in a chair, keep their eyes open, breathe calmly, and avoid movement during data collection. A standard cuff with an inflatable sleeve (12–13 cm wide and 35 cm long) will be used, placed at the level of the heart, with the back and arm properly supported to avoid muscle contraction and BP rises dependent on isometric movement. Two measurements will be taken 1–2 min apart, and the average of these readings will be recorded. If the values differ by ≥10 mmHg, a third measurement will be taken [46]. Measurements will be taken in the morning, and participants will be instructed to avoid caffeine, exercise, and smoking at least 30 min before the measurement [45]. After the test is completed, the data will be downloaded via the Polar Flow Web Service as “.txt” files.

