## Abstract

**Background/Objectives**: Physical exercise (PE) has been shown to have positive effects on the symptoms associated with autism spectrum disorder (ASD). However, there is still no consensus on the most appropriate PE intervention model. With this in mind, we developed a program with the aim of determining the effects of PE on physical fitness, with a view to applying it as a potential treatment. **Methods**: Using an experimental methodology, this research work will recruit 18 institutionalized young people and adults who will be allocated to one of two groups, namely (i) the youth training group and (ii) the adult training group, using low-cost materials. Both intervention groups will perform 90 min of training per session, twice a week, for 12 weeks. Evaluations will be carried out at baseline and month 3. The impact of the exercise program will be assessed based on the variables of anthropometry, body composition, cardiovascular response, and cardiorespiratory fitness. **Results**: The results of this study will contribute to the development of more effective strategies, prescription recommendations, and interventions as a guarantee in future programs of better and greater adherence to PE by institutionalized individuals with ASD. **Conclusions**: In addition, we intend to make the PE program available if it promotes positive effects in the target population.

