Given the increasing prevalence of ASD and the lifelong nature of this condition, it has become imperative to address the health and well-being needs of this population throughout all stages of life. The transition to adulthood is a critical period, marked by significant changes that include a downward trend in the practice of physical exercise, which is widely documented in the literature [17,18,19]. In addition, physical exercise has been recognized as an effective non-pharmacological intervention to improve not only the physical condition but also the behavioral, social, and emotional aspects of people with ASD. To date, only three systematic reviews have included participants aged between 18 and 30 [19,20,21], highlighting a lack of data and clear guidelines for prescribing exercise programs that meet the specific needs of this population. Grouping young people and adults allows us to investigate how physical exercise can be an effective intervention to mitigate the challenges associated with this transition, promoting the maintenance of an active lifestyle.

The aim of this study was to evaluate the effects of a 12-week PE program on the anthropometry, body composition, cardiovascular response, and cardiorespiratory fitness of institutionalized young people and adults with ASD. The following hypotheses will be defined: (i) the youth group (YG) will display a significant improvement in all the variables assessed after a 12-week physical exercise program; (ii) the adult group (AG) will display a significant improvement in all the variables assessed after a 12-week physical exercise program; and (iii) one of the groups (YG or AG) will display a significantly greater improvement in all the variables assessed compared to the other group, after a 12-week physical exercise program.

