### 2.2. Participants

The program will involve volunteers, comprising young people and adults who are institutionalized in a care facility located in Coimbra (Portugal), recruited using the non-probabilistic convenience method. The YG will include individuals aged 10–17, and the AG will include individuals aged 18–65. This division is based on criteria widely recognized in the literature. Adolescence (10–17 years) is a critical phase of development characterized by rapid physiological and cognitive changes [23]. The adult age group (18–65 years), on the other hand, covers a wide range of stages, from early adulthood to middle age [24]. In the first stage, there will be an individual explanation of the objectives and procedures of the study, as well as the potential benefits, risks, and time required for its development. Secondly, participants/family members/legal guardians will sign an informed consent form.

The inclusion criteria will be as follows: (i) having a certified medical diagnosis of ASD (autistic disorder, Asperger’s syndrome, or pervasive developmental disorder without other specification) according to the standards established in the DSM-5-TR [1]; (ii) ages between 10 and 65 years; (iii) a recent history of non-participation in PE programs or similar physical motor activities; (iv) success in performing movements such as running, pulling, and pushing; (v) ability to perform the assessments; and (vi) attendance at least 75% of the total 24 sessions. The exclusion criteria will be defined as follows: (i) individuals who are unable to commit for 3 months; (ii) individuals with other associated pathologies; (iii) clinical contraindications; (iv) inability to walk without support; (v) inability to communicate; (vi) failure to provide signed informed consent; and (vii) individuals over the age of 18 who do not agree to take part in the study. Specific data on socio-economic status and level of education will not be recorded.

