### 2.5. Intervention Assignment and Blindness

Once the initial assessments have been completed, the volunteers will be allocated to the two groups according to their age group. Due to the nature of the intervention, it will not be possible to randomize the sample into groups nor to “blind” participants and the principal investigator.

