#### 3.1.9. Procedures

The intervention study involves seven phases: (i) The first is the design of the PE program. (ii) The second is the promotion of the [+ Life] program, where a poster will be distributed alluding to the importance of the practice of PA by the population under study, identifying the objectives under research, to be distributed by themselves/families/professionals who deal with this issue. A logo will also be created alluding to the whole process, making it the program’s brand image. (iii) The sample will be recruited: participants/parents/guardians will sign an informed consent form, and the entire project will be carried out in accordance with the Declaration of Helsinki [17,18]. (iv) The sample will be divided into the youth training group (YTG) and the adult training group (ATG). (v) An initial evaluation of the groups without blinding the evaluator will be conducted. (vi) A final evaluation of the groups without blinding the evaluator will be carried out. (vii) Data analysis will be performed: descriptive, comparison between groups, comparison before/after intervention, and correlations.

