#### 3.1.11. Statistical Analysis

Descriptive parameters such as the mean and standard deviation will be used in the statistical analysis. The normality of the data will be checked using the Shapiro–Wilk test. Significant differences between groups will be analyzed using the Kruskal–Wallis test, while differences between assessment times will be investigated using the Wilcoxon test. The choice of non-parametric statistics is based on the central limit theorem, which suggests that in order to obtain a normal distribution, a minimum sample size of 30 participants is required [53]. The magnitudes of the differences will be assessed by Cohen’s d effect size [54]. In addition, associations between study variables will be checked using Spearman’s correlation coefficient [55]. The significance level adopted for all analyses will be *p* < 0.05. The data will be processed using the Statistical Package for the Social Sciences (SPSS) software, version 28, Chicago, IL, USA.

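### One cuff size for ages 10 to 65, with no arm circumference recorded, can confound comparisons of blood pressure level and level-based correlations with arm size; comparisons of change are largely protected

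*Protocol article*

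**What the plan says.** Section 3.1.5 (Cardiovascular Response) names one cuff with its dimensions: "A standard cuff with an inflatable sleeve (12–13 cm wide and 35 cm long) will be used". It gives no other size, no rule for matching cuff to arm and no arm measurement. The anthropometry in section 3.1.2 covers height, body mass, BMI and waist. Section 3.1.3 adds segmental lean mass and fat from bioimpedance.

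The cuff serves the whole age range in section 2.2: "The YG will include individuals aged 10–17, and the AG will include individuals aged 18–65". Group membership follows age (section 2.5): "the volunteers will be allocated to the two groups according to their age group". The abstract gives a total of 18 participants and no split.

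For the analysis, section 3.1.9 lists "comparison between groups, comparison before/after intervention, and correlations". Section 3.1.11 adds that "Significant differences between groups will be analyzed using the Kruskal–Wallis test" and that "differences between assessment times will be investigated using the Wilcoxon test", with Spearman coefficients for associations between study variables. Neither section says whether the group test and the correlations use levels or changes. Hypothesis (iii) in the Introduction is about change: "one of the groups (YG or AG) will display a significantly greater improvement in all the variables assessed compared to the other group". Hypotheses (i) and (ii) concern improvement within each group.

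**The concern.** Section 3.1.5 standardises rest, posture, arm support, time of day and repeat readings, but holds the cuff constant while the arm varies. Suppose that a cuff too large for the arm reads low and one too small reads high. The error then rises with arm size. Arm size is likely to differ between youths and adults and to track BMI, waist and segmental fat or lean mass.

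Two kinds of result would be exposed. A youth-versus-adult comparison of blood pressure level could show a difference that is partly cuff error. A correlation between blood pressure level and body composition could appear where there is none. Allocation by age cannot balance arm size, and with no recorded circumference nobody could adjust for it afterwards. Blood pressure level is also one of the factors in choosing step height for the Chester Step Test (section 3.1.6), so the same error could enter the set-up of a fitness test.

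This is a stated rule, not a detail that the article merely leaves to a fuller protocol.

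**Working it through.** **What there is to reproduce.** Nothing. The article gives no blood pressure SD, effect size, arm size or cuff-error figure. The inputs from the document are the single cuff, ages 10–17 and 18–65, allocation by age, N = 18, the Kruskal–Wallis, Wilcoxon and Spearman tests, and a significance level of 0.05. Every other number below is an assumption.

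**1. Bias in level.** Model the error as b × arm circumference, with b in mmHg per cm.

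Spurious group difference = b × gap in mean arm size.
- b = 0.5, gap 6 cm: 0.5 × 6 = 3 mmHg
- b = 1.0, gap 6 cm: 1.0 × 6 = 6 mmHg
- Wider range, b = 0.5 to 2 and gap 2 to 6 cm: 0.5 × 2 = 1 mmHg up to 2 × 6 = 12 mmHg

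**2. Bias in change.** Change = (true week 12 + b × arm at week 12) − (true baseline + b × arm at baseline). With one cuff and a stable arm, the b terms cancel. What remains is b × difference between groups in arm growth.
- No growth: 0 mmHg
- 0.5 cm growth in one group only: 0.5 × 0.5 = 0.25 mmHg, 1.0 × 0.5 = 0.5 mmHg, 2 × 0.5 = 1.0 mmHg

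**3. Induced correlation.** Let e = b × SD of arm size, with true systolic SD 12 mmHg and no true relation. The correlation of measured pressure with arm size is e/√(e² + 12²).
- b = 0.5, arm SD 4 cm: e = 2, and 2/√(4 + 144) = 0.16
- b = 1.0, arm SD 6 cm: e = 6, and 6/√(36 + 144) = 0.45

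The study does not measure arm size. For a body-composition variable, multiply by its correlation with arm size. If that is 0.6 to 0.8, the range becomes 0.16 × 0.6 = 0.10 to 0.45 × 0.8 = 0.36.

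**4. Effect on the planned tests.** A simulation with 1,500 runs per scenario took true pressure as unrelated to group or arm. It assumed a 9 + 9 split, within-group arm SD 3 cm, pressure SD 10 mmHg, SD of true change 8 mmHg, arm gap 2 to 6 cm, and arm growth in one group of 0 or 0.5 cm. The level tests used week 12 for Kruskal–Wallis and baseline for Spearman. The body measure was arm size plus noise of SD 2 cm.

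| Analysis | b = 0 | b = 0.5, gap 6 | b = 1.0, gap 6 | b = 2, gap 6 |
|---|---|---|---|---|
| Kruskal–Wallis on level, false positives | 4–6% | 7% | 15% | 38–45% |
| Kruskal–Wallis on change, false positives | 4–6% | 5% | 4–5% | 5–6% |
| Spearman on level, mean rho | about 0 | 0.17–0.18 | 0.33 | 0.55–0.56 |
| Spearman on level, false positives | 4–6% | 12% | 27–29% | 70–73% |
| Spearman on change, mean rho | about 0 | 0.02–0.04 | 0.04–0.07 | 0.11 |
| Spearman on change, false positives | 5–6% | 4–6% | 5–6% | 7–8% |

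Ranges within a cell cover the two growth settings; the b = 0 column covers all gaps. Across all gaps with b above 0, the false-positive rate for change was 4–7% for the group test and 4–8% for Spearman.

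A t-test approximation with SD 12 mmHg and 9 per group agrees for level: a 3 to 6 mmHg bias is declared significant about 8 to 17% of the time.

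**The case against.** The strongest reply is that the article's hypotheses are about improvement, which is where a fixed cuff does least harm. A reader might infer that the group comparison and the correlations both use levels, and so that the cuff biases the planned comparison outright. The documents do not support that. Hypothesis (iii) compares improvement, and sections 3.1.9 and 3.1.11 name tests without saying what they are applied to. If the group test is run on change, its error rate is about nominal in step 4. This part of the reply stands.

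The reply is also right on three narrower matters. The documents do not show that the cuff misfits anyone: the article calls it standard, not adult-size, and the linear error model allows no range of arms in which the cuff simply fits. The 0.16 to 0.45 in step 3 should not be read as a correlation with body composition, which would be smaller. And no hypothesis rests on the correlations.

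One caution concerns the remedy. Choosing a new cuff at week 12 would put an instrument change inside the before/after comparison, which a constant cuff protects. Any fix has to avoid that where it can.

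What the reply does not remove is that the text allows level-based analyses, lists the group comparison separately from the before/after comparison, and defines no change score.

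**Conclusion.** The point holds in limited form, as a minor one. The article fixes one cuff size across ages 10 to 65, records no arm circumference and forms groups by age. If cuff error varies with arm size, blood pressure levels compared between the groups, and level-based correlations with body composition, can be confounded by arm size.

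Under the assumed 0.5 to 1.0 mmHg per cm and a 6 cm gap, the artefact in level is 3 to 6 mmHg, enough to raise the false-positive rate of a level-based Kruskal–Wallis test from 5% to roughly 7–15%. Under the assumptions of step 3, the spurious correlation with body composition is about 0.10 to 0.36. These figures show scale only; the slope, gap and SDs are not in the documents.

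The before/after tests and a between-group test of change are largely protected, provided that the same cuff is used and the arm is stable. It would be wrong to conclude that the cuff invalidates hypotheses (i) to (iii).

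**What to change.** In section 3.1.5, replace the single fixed size with a rule:
- Measure mid-upper-arm circumference at baseline with the tape already used for waist, and choose the cuff from it.
- Record the circumference and the cuff size.
- Recheck the arm at week 12, keep the same cuff for that participant where it still fits, and flag any switch so that its effect on the before/after comparison can be examined.

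In section 3.1.11, state that the between-group test is run on change from baseline, in line with hypothesis (iii), and say whether the correlations use levels or changes.

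The cost is one or two extra cuffs, one brief measurement at each of the two existing assessments, and a few sentences of text. No extra visit or staff is needed.

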#### 3.1.6. Cardiorespiratory Fitness

##### Six-Minute Walk Test

This is a submaximal test, which aims to assess the distance an individual is able to walk for 6 min, in which two tests are required, with a minimum interval of 30 min between them. The usual medication and walking aids should be maintained. There should be no warm-up period. The individual should sit at rest in a chair, close to the starting position, for at least 10 min before the test begins. During this time, it should be checked whether the individual meets any of the contraindications for taking the test [47]. When it is implemented, the following will be recorded: peripheral oxygen saturation (SpO^2^), SBP, DBP, HHR, perceived dyspnea, and lower limb fatigue (Modified Borg Scale).

